# A Dietary Supplement for Mood Symptoms in Early Postpartum: A Double Blind Randomized Placebo Controlled Trial

[figure not shown]

**Figure 7.** Free Tyrosine in Common Infant Formulas and in Breast Milk After Oral Tyrosine Supplementation. Mean and standard deviation are presented. Free tyrosine in breast milk even with the highest dose of 10g oral tyrosine was significantly lower than free tyrosine in the 2 extensively hydrolyzed infant formulas tested (Alimentum and Nutramigen A+) (Analysis of variance, post-hoc comparisons, Fisher's least significant difference (LSD),  $p<0.005$ ) and similar to partially hydrolyzed formulas tested (Good Start 0+ and Good Start 2).

[figure not shown]

**Figure 8.** Free Tryptophan in Common Infant Formulas and in Breast Milk after Oral Tryptophan or Alpha-lactalbumin (a-lac) Supplementation. To capture the variation in free breast milk levels, the y axis was broken to 3 segments. Mean and standard deviation are presented. Free tryptophan in breast milk even with the highest dose of 4g tryptophan was comparable to non-hydrolyzed formulas, and significantly lower than extensively hydrolyzed formulas (Nutramigen A+ and Alimentum) (analysis of variance, post-hoc comparisons, Fisher's least significant difference (LSD),  $p<0.005$ )

## **2.8. The Effect of the Proposed Dietary Supplement on Mood Symptoms in Early Postpartum in an Open Label Trial**

**Rationale for Amounts Tested:** Based on the optimal doses found in the studies investigating the effect of oral tryptophan and tyrosine on their concentrations in breast milk, we continued on investigating the ability of a dietary supplement containing 2 grams of tryptophan, 10 grams of tyrosine along with blueberry extract/juice as an antioxidant on reducing the intensity of postpartum blues. Tyrosine supplement at the dose of 10 grams was chosen to be tested since based on our previous clinical trial this dose did not have any effects on total tyrosine levels in breast milk, was significantly increased in maternal plasma and was extremely well tolerated. Moreover, most of the investigations of tyrosine with similar doses support its ability to protect against adverse cognitive effects of stress: Under conditions of cold stress, noise stress, and hypoxic stress, single doses of 100mg/kg, 150mg/kg and 300mg/kg were helpful in creating resilience, based upon unimpaired performance upon cognitive tasks, mainly in the area of working memory and again these doses were also well tolerated. Tryptophan supplement at the dose of 2 grams was chosen to be tested since based on our previous clinical trial this dose did not have any effects on total tryptophan levels in breast milk, was significantly increased in maternal plasma and was extremely well tolerated. Although 4 grams did not increase total tryptophan in breast milk, it was associated with nausea in half of the subjects receiving that dose. Moreover, the changes in plasma tryptophan between the groups receiving 2g or 4g were minimal, suggesting limited advantage of the greater dose. In a study administration of 0.8 grams of tryptophan, tryptophan was able to modestly, but significantly, improve mood in healthy subjects. We acknowledge that it has been proposed that higher doses of tryptophan are necessary to reduce symptoms of major depressive episodes, although, . Hence, 2g, while lower than the 4g dose previously tested, may achieve at least modest benefit for mood as it is well tolerated, has no effects on overall tryptophan in breast milk and may have effects upon mood in healthy people.

### **Rationale for Postpartum Blues Target and Recent Advances in Quantitation of Postpartum Blues:**

We chose postpartum blues because when postpartum blues are more severe, they are associated with greater risk of postpartum depression (so reducing the intensity of postpartum blues should lead to reduced risk of PPD). We have also improved upon existing methods to measure the severity of postpartum blues through use of depressed mood induction and standardized mood rating scales after the mood induction, which is a standardized sensitive approach for measuring mood dysregulation. We find that after sad mood induction, women who are day 5 postpartum and healthy women within the first 18 months postpartum with vulnerability to crying (but did not have clinical depression) clearly have greater shift towards depressed mood on visual analogue scale (**figure 9**) and the profile of mood states as compared to healthy women who are not in day 5 postpartum and do not have crying spells with in the first 18 months postpartum respectively. We have advanced symptom targeting through improving upon existing methods to measure the severity of postpartum blues: We apply depressed mood induction and standardized mood rating scales after the mood induction, which is a standardized sensitive approach for measuring mood dysregulation, particularly in early postpartum.

## A Dietary Supplement for Mood Symptoms in Early Postpartum: A Double Blind Randomized Placebo Controlled Trial

[figure not shown]

**Figure 9.** Stronger Elevation in Depressed Mood Scores in Visual Analog Scale (VAS) in Day-5 Postpartum Women. Univariate analysis of covariance showed a significant group effect on the change in VAS mood scores after the sad mood induction procedure ( $F(3,41)=22.45, p<0.005$ )

**Results of the Previous Open Trial:** We find that after sad mood induction, women who are day 5 postpartum, not taking the proposed dietary supplement, clearly have greater shift towards depressed mood on visual analogue scales (**figure 10**) and the profile of mood states as compared to healthy women who are in day 5 postpartum taking the proposed dietary supplement. The results of the open label trial, which is nearing completion, indicate that the dietary supplement was able to significantly attenuate the intensity of postpartum blues in day-5 postpartum women compare to those not receiving any dietary supplement. The results demonstrated that receiving the dietary supplement was significantly associated with minimal or no change in mood as measured by the VAS mood scores after sad mood induction. VAS depressed mood score change after the sad MIP was  $50.03 \pm 16.29$  in controls and  $1.37 \pm 8.47$  in supplemented group. The effect size was 5.4.

## A Dietary Supplement for Mood Symptoms in Early Postpartum: A Double Blind Randomized Placebo Controlled Trial

[figure not shown]

**Figure 10.** Stronger Elevation in Depressed Mood Scores in Visual Analog Scale (VAS) in Day-5 Postpartum Women not Taking the Dietary Supplement. Analysis of variance found significant elevation in depressed mood scores as measured by VAS in day-5 postpartum women not taking any supplements compared to day-5 postpartum women taking the dietary supplement ( $F(1,29) = 110.91, p < 0.001$ ).

**Why advance from an open trial to a randomized double blind placebo controlled trial?** Now in this proposed study we would like to investigate if a dietary supplement given in double blind placebo controlled RCT study can prevent the shift in sad mood in these two groups. The reasons to pursue investigating the effect of the proposed dietary supplement in a double blind placebo controlled trial include: 1) Significant positive effect of 5.4 observed in the recent open-label trial study, 2) The proposed dietary supplement has been well tolerated by all subjects and no side effects were observed, 3) We have an available placebo which was developed and tested in an ongoing separate clinical trial in our group, 4) A double blind randomized placebo controlled trial is expected in science. 5) If the combination of ingredients is someday developed as a dietary supplement, it is expected that a rigorous scientific process such as a randomized double blind placebo controlled trial is needed to demonstrate efficacy.

### 3. Hypothesis:

Sadness after depressed mood induction during postpartum blues will be attenuated in those receiving the dietary supplement (tryptophan, tyrosine and blueberry juice/extract) compared to placebo.

## **4. Objectives:**

### *Primary endpoint:*

To assess the ability of the dietary supplement to reduce the intensity of postpartum blues in a double blind RCT.

### *Secondary endpoint:*

To assess the ability of the dietary supplement to prevent postpartum depression up to 6 months postpartum

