## 2. Background

### 2.1. Importance of Postpartum Depression

**Overview of Mood Disturbances in the Postpartum Period:** There are three types of mood disturbances involving sadness in the postnatal period. One is the “baby blues” or maternity blues which is common (occurring up to 75% of the time) and transient finishing within the first week postpartum. The second is a major depressive episode (MDE) with postpartum onset (“postpartum depression”) which is defined as a MDE that occurs within the first four weeks after delivery. **Greater severity of the common healthy range baby blues/maternity blues is associated with greater risk for subsequent clinical level postpartum depression**. The third is postpartum psychosis (which may be accompanied by depressive symptoms). The third condition is rare occurring in 0.1 to 0.2 per cent of deliveries and is strongly associated with presence of bipolar disorder.

**Importance of Clinical Level Postpartum Depression (MDE with Postpartum Onset):** Postpartum depression (PPD), defined as a MDE starting within the first year after giving birth, is highly impactful, being the most common complication of childbearing with a prevalence rate of 13 %. Consistent with this, the World Health Organization has identified major depressive disorder (MDD) as the leading cause of death and disability worldwide. A MDE in early postpartum can lead to serious consequences: During the first postpartum year, presence of psychiatric illness is associated more than a 10 fold risk of suicide and women who have experienced MDE with postpartum onset are at greater risk of having further MDE both following future deliveries and at times unrelated to childbirth. Also, MDE with postpartum onset may last for years, and has deleterious effect on infant motor and social development and the health of other children in the family and the partner.

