## **5. Methods:**

### **5.1. Subject criteria**

One hundred forty pregnant women who are healthy and have no history of MDE will be recruited during their third trimester and such that at least 100 completing subjects will be enrolled to complete the study. Participants will be recruited by advertisement (see end of section 5.1 for further detail regarding advertising). Subjects expressing interest at earlier times in pregnancy will have their initial visit booked in the third trimester (i.e. in person completion of screening questionnaires to rule out a psychiatric disorder and final verification of other requirements). Subjects will randomly be assigned to placebo or active supplement in a double blind manner within blocks of 2, 4, 6, 8 or 10 subjects. Block size will be randomly selected using standard randomizing software. The supplements/placebo will be taken at 4 time points, starting on day 3 postpartum night to day 5 postpartum morning (See table 2 for full schedule). Subjects will receive either the dietary supplement or a placebo that matches in taste and colour (as verified by independent manufacturer and investigator for visual and taste testing during placebo product development) (this has already been created). On day 5 postpartum, participants will be seen for a single visit (at their house).

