**Timing of administration of study products:**

- Night of day 3 postpartum: Participants will mix one pouch of active or placebo extract with one active or placebo juice and drink at once
- Morning of day 4 postpartum: Participants will mix one pouch of active or placebo extract with one active or placebo juice and drink at once
- Night of day 4 postpartum: Participants will mix one pouch of active or placebo extract with one active or placebo juice and take the 2 grams of tryptophan (2 capsules of 1 gram tryptophan each) or placebo with the beverage
- Morning of day 5 postpartum (main study day): Participants will mix one pouch of active or placebo extract with one active or placebo juice and take the 10 grams of tyrosine (20 capsules of 500 milligrams tyrosine each) or placebo with the beverage

**Blinding:** The ratio of active treatment to placebo will be 1:1. Since the supplement appears likely to prevent postpartum blues on an individual case level, additional care is being taken in regards to the randomization process. The assignment of placebo supplement or active supplement will be done by the research pharmacy department who randomizes subjects evenly to each condition within blocks of 2, 4, 6, 8 or 10 subjects. Each block size will be randomly selected using standard randomizing computer software. Then, for each block subjects will be randomly selected to either protocol. For example, if a block is of size 8, four ordered numbers will be randomly assigned to one group and the remaining 4 numbers will be assigned to the other group. Each subject will be recorded in relation to a code number. The administration of the mood induction procedure and the supplement will be done on day 5 postpartum by an expert who is blinded to both.

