### **5.4.7. Procedures after Day 5 Postpartum**

There will be four follow-up phone calls: Day-10 postpartum, 1 month postpartum, 3 months postpartum and 6 months postpartum. Follow-up phone calls will involve few general questions regarding participant's mood and feeling over the past few weeks, which involve completing the questionnaires SCID-RV for DSM-5 (mood (current MDE, current manic episode, current cyclothymic disorder, current persistent depressive disorder), anxiety disorders and OCD sections), HAM-D, EPDS, CES-D Stein blues Scale, Kennerley and Gath Blues Scale and BDI. Since history of COVID-19 may also affect mood state, participants will also be asked if they were diagnosed with COVID-19 at each phone call. Even though some of these questionnaires are self report, all of these questionnaires will be conducted over the phone by the study co-investigator, study RA, or research student. For each follow-up phone call at least 5 attempts will be done in the subsequent 10 days after scheduled time points (we do not leave messages). If the participant is unavailable, the 1 month postpartum, 3 month postpartum, and 6 month postpartum follow-up phone calls may be completed up to one week after the 10 day window.

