## **5.5 Statistical Analysis**

Our primary analysis will be the use of repeated measures analysis of variance with the visual analogue scale of depressed mood as the repeated measure (before and after the sad MIP) and active condition versus placebo as the between subject measure.

Our secondary analysis will be the change in depression scores on profile of mood state (POMS) scale, using repeated measures analysis of variance with the POMS score as the repeated measure (before and after the sad MIP) and active condition versus placebo as the between subject measure.

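### The six-month postpartum-depression endpoint is diagnosed only as a current episode at four calls, so episodes that begin and remit between calls can be missed; sections 4 and 5.5 also use 'secondary' for different outcomes

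*Protocol*

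**What the plan says.** Protocol section 4 (Objectives) lists one secondary endpoint: "To assess the ability of the dietary supplement to prevent postpartum depression up to 6 months postpartum". POMS does not appear there.

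Section 5.5 (Statistical Analysis) names one secondary analysis: "Our secondary analysis will be the change in depression scores on profile of mood state (POMS) scale", compared before and after the sad mood induction on day 5. PPD does not appear there. Section 5.6 gives power for the VAS and POMS only.

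Section 5.4.7 schedules follow-up calls at day 10 and at 1, 3 and 6 months. The diagnostic part consists of "completing the questionnaires SCID-RV for DSM-5 (mood (current MDE, current manic episode, current cyclothymic disorder, current persistent depressive disorder", plus the anxiety and OCD sections. The same calls include general questions on mood over the past few weeks, and the HAM-D, EPDS, CES-D, BDI, Stein and Kennerley-Gath scales. Section 5.4.3 gives the BDI and EPDS a seven-day recall.

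On size, section 5.1 says "One hundred forty pregnant women who are healthy and have no history of MDE will be recruited", "such that at least 100 completing subjects will be enrolled to complete the study". Section 5.2 says "The ratio of active treatment to placebo will be 1:1".

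**The concern.** An endpoint that runs up to 6 months postpartum is naturally read as cumulative: did the woman have an MDE at any time in that period? The diagnostic instrument is worded for the moment of the call. A SCID limited to current episodes at four dates measures four point prevalences. A woman who was depressed and recovered in the longer gaps can be recorded as never having had PPD. That lowers the case count in both arms, in a trial where few cases are expected. If the supplement changed how long episodes last rather than whether they occur, the current-only count would mix the two effects.

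The labels are a separate, smaller matter. A reader of section 4 would look for PPD as the secondary result; a reader of section 5.5 would look for POMS. Nothing says how the two relate, so it is unclear which outcomes were prespecified as secondary.

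**Working it through.** **1. Ascertainment**

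The table sets the intervals between calls beside the recall stated for what is asked at the later call.

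| Interval | Approximate length | What reaches back into it |
|---|---|---|
| Delivery to day 10 | 10 days | current SCID; 7-day BDI and EPDS; past few weeks (general questions) |
| Day 10 to month 1 | about 3 weeks | the same; largely spanned by the general questions |
| Month 1 to month 3 | about 2 months | the same; most of the interval not covered by the 7-day scales |
| Month 3 to month 6 | about 3 months | the same; most of the interval not covered by the 7-day scales |

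The protocol does not say how far back a current episode may reach, so a range has to be assumed:

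- Look-back of 7 days, as for the BDI and EPDS: about 61 − 7 = 54 days uncovered between months 1 and 3, and about 91 − 7 = 84 days between months 3 and 6.
- Look-back of a full month, a generous reading of the past few weeks: 2 − 1 = 1 month and 3 − 1 = 2 months uncovered.

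Under either assumption an episode lying wholly inside the uncovered stretch is not diagnosed. The scales and general questions are not a SCID diagnosis, so even within their recall they do not by themselves establish an MDE. How many episodes are lost depends on their duration and timing, which the document does not give.

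**2. Labels**

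| Section | What is called secondary | When measured |
|---|---|---|
| 4 | PPD | up to 6 months |
| 5.5 | POMS depression change | day 5, around the sad induction |

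Neither section mentions the other's outcome.

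**3. What the sample can say about PPD**

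The protocol states no power for PPD, so there is no figure to reproduce. Inputs:

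- Per arm: 100 completers at 1:1, so 100/2 = 50.
- Control rate: p1 = 0.13, the prevalence in section 1.
- Effect: a halving, p2 = 0.065 (assumed).
- Alpha: two-sided 0.05 (assumed).

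Expected cases are 50 × 0.13 = 6.5 on placebo and 50 × 0.065 = 3.25 on active.

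Power from the two-proportion formula with pooled null variance, pooled rate 0.0975:

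- Null term: 1.960 × √(2 × 0.0975 × 0.9025) = 0.822
- Alternative SD: √(0.13 × 0.87 + 0.065 × 0.935) = 0.417
- z = (√50 × 0.065 − 0.822)/0.417 = −0.87, so power is 19%

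Exact enumeration of two binomials gives 9.8% for Fisher's test and 19% for the uncorrected chi-square. For 80% power: n = (0.822 + 0.842 × 0.417)²/0.065² ≈ 326 per arm.

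The 95% confidence interval half-width for the risk difference is 1.96 × √(0.1131/50 + 0.0608/50) = 0.116, or 11.6 percentage points against an expected difference of 6.5.

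Sensitivity to the control rate, halving in each row:

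| Control rate | Power at 50 per arm (formula) | Fisher | Per arm for 80% |
|---|---|---|---|
| 5% | 10% | 1% | 906 |
| 10% | 16% | 6% | 435 |
| 13% | 19% | 10% | 326 |
| 20% | 29% | 20% | 199 |

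With all 140 recruited women analysed (70 per arm), power for 13% v 6.5% is 25%.

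**The case against.** **The two labels may be compatible.** Section 4 ranks objectives and section 5.5 ranks analyses. Section 5.4.6 pairs the VAS and POMS as mood measures around the induction, so POMS can be read as a second measure of the primary objective. That is a fair reading. It makes this a labelling gap rather than proof of rival secondary endpoints, but the protocol does not state the reading and should. The absence of a PPD method from section 5.5 is not counted here, since it may be in an analysis plan.

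**Current-only is not the whole of follow-up.** The scales and general questions are collected at every call, and new cases can be added up across the four calls. This stands in part: delivery to month 1 is reasonably covered, and it would be too strong to say that every between-call episode is lost. It does not close the 2- and 3-month gaps, and a running total of current diagnoses still undercounts.

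**A secondary endpoint need not be powered.** This stands in full. The protocol claims no PPD power, its hypothesis concerns only sadness after induction, and section 1 describes PPD prevention as a multistep process.

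Three stronger readings are tempting but not supported:

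- *A null is near-certain.* For a halving of 13% the chance of a non-significant result is 81% (chi-square) to 90% (Fisher). Complete prevention would be detected by Fisher's test about 65% of the time.
- *A chance split of 6 v 0 would be reported as prevention.* Such a split is significant (Fisher p = 0.027), but no passage says it would be presented that way. With no true effect and a 13% rate in both arms, 6 or more cases on placebo against none on active has probability of about 0.06%; all Fisher rejections favouring active total about 1.1%.
- *The protocol contradicts itself on the onset window.* Section 2.1 has PPD both as "defined as a MDE that occurs within the first four weeks after delivery" and as "defined as a MDE starting within the first year after giving birth". Both are background text; section 4 sets the trial's window at 6 months.

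**Conclusion.** The point holds in a limited form. The endpoint covers the whole period to 6 months, while the diagnosis is made only for episodes current at day 10 and months 1, 3 and 6. Diagnosable episodes confined to the gaps between months 1 and 3 or 3 and 6 can be missed, and cumulative incidence is not captured. The size of the loss is unknown. Separately, sections 4 and 5.5 attach the word secondary to different outcomes without linking them.

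The power of 10% to 19% rests on 50 completers per arm, the protocol's 13%, an assumed halving and an assumed two-sided 0.05. The 13% is a general figure. The trial recruits women without a history of MDE, which section 2.2 places among the strongest risk factors, so the true rate may be lower and power lower still; by how much is not in the document. These figures govern how the PPD result should be read. They do not make it wrong to keep PPD as a secondary endpoint, and whether to call it secondary or exploratory is the sponsor's choice. A reader might infer that the trial has nothing to say about PPD. That goes too far: it can give an estimate with a wide interval.

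Nothing here affects the primary VAS analysis.

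**What to change.** - **Section 5.4.7:** at each of the four existing calls, ask the SCID MDE items for the whole interval since the last contact, with the date of onset, as well as for the present.
- **Section 4:** define a PPD case as a SCID MDE with onset after delivery and by 6 months.
- **Sections 4 and 5.5:** list the POMS depression change in section 4 and say how it relates to the primary objective and to PPD, so that the two sections agree.
- **Reporting:** give PPD as a risk difference with a 95% confidence interval, and state that a non-significant result is not evidence of no effect.

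The cost is a few extra minutes per call, some recall error over intervals of up to about 3 months, and wording changes. No visits or participants are added. The interval questions need to be in place before follow-up, because a missed episode is hard to recover afterwards.
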